### Secondary objectives

The secondary objective of the study is to determine whether the treatment is cost-effective compared to the wait-list condition and to examine other exploratory outcome measures. The questionnaires will be collected at screening, first treatment session and last treatment session. Follow-up questionnaires will be collected at 6 and 12 months post-treatment. The exception is change in diagnoses which will be evaluated by clinical interview at screening, before the first treatment session and after the last treatment session.

Measurements for the study’s secondary objective:
Changes in quality of life as measured by the EQ-5D-5L [37]Changes in metacognitions as measured by the Metacognitions Questionnaire 30 (MCQ-30) [38]Changes in bullying and victimisation as measured by the Negative Acts Questionnaire [39].Changes in work-related self-efficacy as measured by the Return to Work Self-Efficacy questionnaire (RTW-SE) [40].Changes in resilience as measured by The Resilience Scale for Adults (RSA) [41]Changes in subjective health complaints as measured by the Subjective Health Complaints questionnaire (SHC) [42].Change in diagnoses as measured by the Mini-International Neuropsychiatric Interview (M.I.N.I.) [43].

### Other outcome measures

Secondary analysis related to the onset of COVID-19 (time frame: from pre-treatment to post-treatment (12 weeks) and 6 months and 1 year follow-up). Sub-analyses will take into consideration the onset of COVID-19 in Norway by the middle of March 2020. In addition to potentially influencing depression and anxiety symptoms, COVID-19 may have influenced the work situation for participants. Thus, it is important to explore if this is the case for those recruited to the project after the outbreak of the pandemic. The COVID-19 pandemic hit during the project, and it may have influenced initial levels of anxiety and/or depressive symptoms. We therefore think it would be important to explore if those included prior to and after the onset are systematically different regarding symptom severity. Also, the pandemic with a subsequent lock-down of many central society services affected many persons work situation. Many in service occupations lost their jobs and others were put on unpaid leave. Regarding the output variable return to work, it is important to check if many of the patients were in this situation. We therefore included a questionnaire that asks patients included during the Covid pandemic whether their working situation, sick leave or income was affected by the pandemic.

### Study design

The study is an RCT comparing MCT and work-focused interventions given immediately after screening (< 1 week after assessment) with a wait-list condition. We chose a waitlist design as a “no treatment” control group is not feasible due to ethical reasons, and comparison with another active treatment was not feasible due to practical reasons. The intervention will be given as manualised treatment based on diagnostic-specific MCT as specified in the manual from 2009 by Wells [44]. Work-focused interventions will be based on the work module used in Lagerveld’s study but adjusted for a Norwegian context and MCT [18].

A summary flowchart of the procedure is found in Fig. 1. Treatment duration is up to weekly 12 sessions, but as the study takes place in a national health service outpatient clinic, the number of sessions may vary. The treatment primary outcome is measured at end of treatment or session 12 if treatment duration is longer, whichever comes first. In all, 240 patients who are on sick leave due to anxiety or depression at the time of enrolment will be recruited. The study uses a block randomisation with a stratification based on gender and degree of sick leave to ensure an equal balance of gender and sick leave across the conditions. Degree of sick leave indicates the percentage of ordinary working hours. Someone working half their normal number of hours would thus be on 50% sick leave. An equal number of patients are randomised to the treatment and wait-list condition. The waitlist condition group is subdivided into two equal groups that wait either 8 or 12 weeks before treatment, because in the sample there will be variation in the duration of the treatment intervention. The registry data will benchmark the current study against previous studies that have used CBT with regards to RTW. The maximum waiting time of 12 weeks is identical to the average waiting time at the clinic, to ensure that participation in the study does not delay treatment for patients. The reason for differentiating the waitlist condition is twofold. First, Norwegian law dictates that patients with moderate to severe depressive episodes should not wait longer than 8 weeks. Secondly, it is important to investigate if the duration of waiting in itself accounts for differences in change, e.g. whether shorter or longer waiting times improves outcomes.

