### Randomisation and blinding

After the initial screening session, eligible patients will be randomised using WebCRF, a web-based program provided by the Unit for Applied Clinical Research at the Norwegian University of Science and Technology (NTNU). The block randomisation is stratified on gender and degree of sick leave. The study will include 240 patients in all. Half of the patients will be allocated to the treatment condition (*n* = 120) and the other half to the wait-list conditions (*n* = 120). Half of the patients in the wait-list condition wait 8 weeks, the other half wait 12 weeks before commencing treatment. Because the treatment is offered in an ordinary outpatient clinic, the duration of the treatment will vary. To control for potential differences in treatment duration the wait-list condition also contained two different conditions.

Guidelines from the Norwegian Directorate for Health and Social Affairs state that patients who fulfil the criteria for a moderate depressive episode according to ICD-10 have the right to specialised health care within 8 weeks of referral [45, 46]. Thus, patients with this diagnosis will be allocated evenly between the treatment condition and the 8-week waiting condition. No patients with moderate depressive episode will be allocated to the 12-week waiting condition due to Norwegian law.

The randomisation procedure is performed by administrative personnel who otherwise are not involved in the patient’s treatment. Clinicians are not involved in the randomisation procedure. The initial assessment session is carried out by a different therapist than the one the patient sees for treatment. Blinding the treatment therapist to group allocation is not doable for logistical reasons (e.g. date of journal documents). Assessment of diagnosis at end of treatment using the Mini-International Diagnostic Interview is carried out by an independent clinician who has no prior contact with the patient.

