### Sample size estimate

Sick leave will be operationalised as a percentage of sick leave collected both from the national registry and self-report. To evaluate the intervention versus wait-list condition, the percentage of sick leave status of the intervention group will be compared at end of treatment to the status of the control group at the end of the waiting period. The minimum expected effect is that of the treatment reported in the naturalistic follow-up study at the same clinic [56]. Data from this study showed a self-reported full RTW response rate of 0.41 in the intervention group versus 0.26 in the wait-list control group, with a pooled standard deviation of 0.4 [34]. Given this result, to detect differences in a dichotomous outcome variable we would need approximately 120 in each treatment group to have an 80% chance of detecting a significant difference at a two-sided significance level of 0.05 [63]. For the anxiety and depressive symptoms, detecting a 5 point difference between intervention and waitlist control group using a pooled standard deviation of 6.95, we need approximately 31 participants in each of the group in order to have an 80% chance of detecting a significant difference at a two-sided significance level of 0.05 [28, 64].

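### An all-patient comparison of the 8-week and 12-week waits is confounded with diagnosis, because every wait-listed patient with a moderate depressive episode waits 8 weeks and none waits 12

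*Protocol article*

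**What the plan says.** All references are to the Methods of the protocol article.

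- **Study design** gives two reasons for having two waiting times. The first is a legal limit on waiting for patients with more severe depressive episodes. The second is that "it is important to investigate if the duration of waiting in itself accounts for differences in change".
- **Randomisation and blinding** makes the available arms depend on diagnosis. For a moderate depressive episode, "patients with this diagnosis will be allocated evenly between the treatment condition and the 8-week waiting condition", and "No patients with moderate depressive episode will be allocated to the 12-week waiting condition due to Norwegian law".
- The same section fixes the sizes. "The study will include 240 patients in all", 120 in treatment and 120 on the wait-list, and "Half of the patients in the wait-list condition wait 8 weeks, the other half wait 12 weeks before commencing treatment", which is 60 and 60.
- On strata, it says "The block randomisation is stratified on gender and degree of sick leave". Study design names the same two factors: "block randomisation with a stratification based on gender and degree of sick leave".
- **Eligibility criteria** admit mild to moderate depressive disorders. The expected number with a moderate episode is not given.

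Nothing in the article confines the 8 v 12 week comparison to patients who could be given either wait, or adjusts it for diagnosis. The Discussion treats the 8-week rule as a limit on the length of the wait and on comparison with other countries. It does not mention it as a confounder of waiting time.

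**The concern.** To learn whether waiting time in itself matters, the two waiting groups must be comparable in everything else. Here one group holds all the wait-listed patients with a moderate depressive episode and the other holds none. Depression severity bears directly on the BDI-II, one of the primary outcomes, and patients who start higher may change more through regression to the mean alone. A difference between the waits could therefore be produced by diagnosis, and a real effect of waiting could be hidden by it.

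Two statements also need reconciling with the diagnosis rule. The factor that decides which arms are open to a patient is not among the named strata. And an equal split of the wait-list does not follow from the rule without a compensating imbalance among the other patients, which the article does not describe.

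**Working it through.** The article gives no effect size, power or sample size for the 8 v 12 week question, so there is no figure to reproduce. The check is allocation arithmetic.

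**Inputs from the article:** N = 240; treatment 120; wait-list 120, split 60/60; moderate episodes divided evenly between treatment and the 8-week wait, none to 12 weeks. **Assumed:** m, the number with a moderate episode, shown over a range.

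**1. Equal waits (60/60) kept as stated.**
- Moderate patients in the 8-week group: m/2, a share of (m/2)/60. In the 12-week group: 0.
- Others in the 8-week group: 60 − m/2. Others in the 12-week group: 60.
- Share of wait-listed others sent to 12 weeks: 60/(120 − m/2).

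| m | moderate share, 8 v 12 weeks | others, 8 v 12 weeks | wait-listed others sent to 12 weeks |
|---|---|---|---|
| 40 | 20/60 = 33% v 0% | 40 v 60 | 60/100 = 60% |
| 80 | 40/60 = 67% v 0% | 20 v 60 | 60/80 = 75% |
| 100 | 50/60 = 83% v 0% | 10 v 60 | 60/70 = 86% |
| 120 | 60/60 = 100% v 0% | 0 v 60 | 60/60 = 100% |

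Above m = 120 the moderate patients alone exceed 60 in the 8-week group, so equal waits are impossible.

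**2. Other wait-listed patients split evenly instead.** There are 120 − m/2 of them, so 60 − m/4 go to each wait. The 8-week group has m/2 + 60 − m/4 = 60 + m/4 patients and the 12-week group 60 − m/4. At m = 80 this is 80 v 40, which is not half and half. The confounding is smaller but remains: 40/80 = 50% moderate against 0%.

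**3. What this could do to the comparison (illustration).** Suppose waiting time has no effect and moderate patients change by D points more or less than the others. The crude 60/60 difference is then biased by D × m/120. Take D = 3 (assumed) and borrow the symptom-score SD from the Sample size estimate ("using a pooled standard deviation of 6.95"). The standard error is 6.95 × √(2/60) = 1.27. With a two-sided 5% z-test:

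| m | bias (points) | chance of a significant result |
|---|---|---|
| 24 | 0.6 | 7.6% |
| 40 | 1.0 | 12% |
| 80 | 2.0 | 35% |
| 120 | 3.0 | 66% |

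The nominal rate is 5%.

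**4. The main comparison.** Treatment holds m/2 moderate patients of 120, and the pooled wait-list holds m/2 of 120. The shares are equal for every m up to 120, so diagnosis does not confound this contrast.

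**5. The restricted comparison.** Among patients without a moderate episode the groups are 60 − m/2 v 60 under equal waits. The difference detectable with 80% power is (1.96 + 0.84) × 6.95 × √(1/n₈ + 1/n₁₂), where n₈ and n₁₂ are the two group sizes:
- no moderate patients, 60 v 60: 3.6 points;
- m = 40, 40 v 60: 4.0 points;
- m = 80, 20 v 60: 5.0 points.

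**The case against.** The best defence is that no such test is planned. The 8 v 12 week question appears once, as a reason for the design. It is absent from the hypotheses, the objectives, the sample size and the analysis section, and the article refers to a separate pre-specified analysis plan where population and covariates would be set. This stands to the extent that the article states an aim and not a test, and nobody can say that an unadjusted comparison will be run. It does not dispose of the point, because the stated allocation rule defeats the stated aim unless the comparison is restricted, and nothing shown restricts it.

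The second defence is that the diagnosis rule is disclosed and amounts to a separate allocation scheme, so its absence from the strata is partly a matter of labelling. That is fair. Listing diagnosis as a stratum would not rescue the all-patient contrast either, because there are no moderate patients at 12 weeks.

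Three stronger readings are tempting, and the document does not support them:
- **That the 8 v 12 comparison is not randomised at all.** Patients without a moderate episode can be allocated to either wait, so a valid contrast exists within the design.
- **That most patients without a moderate episode are pushed into the 12-week wait.** This holds only among those on the wait-list. Of all such patients the share is 60/(240 − m): 30% at m = 40, 37.5% at m = 80, and at most 50% for m up to 120.
- **That the main treatment effect is biased by this rule.** Under even allocation the arms have the same moderate share. Adding the factor to the primary models is good practice and may help precision, but no loss has been quantified.

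**Conclusion.** The point holds for the secondary question about waiting time. By the article's own rule, an all-patient comparison of 8 with 12 weeks cannot separate waiting from diagnosis. The zero moderate share in the 12-week group is fixed by design. The share in the 8-week group depends on m, which is not stated: 33% at m = 40 and 67% at m = 80 with equal waits. The size of any bias also depends on D, which is assumed here, and on applying the planning SD to this contrast, so the error rates above are illustrations and not forecasts. The half-and-half split and the diagnosis rule can both be met only up to m = 120, and only with an uneven and undescribed allocation of the other wait-listed patients. The primary comparison is not put in doubt. This is a cheap improvement.

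**What to change.** Three changes of wording in the analysis plan and the report:

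1. State that any comparison of 8 with 12 weeks is confined to patients without a moderate depressive episode, the only ones who could be allocated to either wait. Adjusting an all-patient model for diagnosis would draw its waiting-time contrast from these same patients, so restriction gives up no usable information.
2. Include moderate episode (yes/no), with gender and degree of sick leave, as a covariate in the primary models, since it governed allocation.
3. Reconcile Study design with Randomisation and blinding on the equal split of the wait-list by giving the allocation numbers for each wait by diagnosis.

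The cost is small. Diagnosis is assessed at screening, so no new data are needed. Recruitment is complete, and nothing about patients' waiting or treatment is affected. The price is a smaller and less precise waiting-time contrast, for example 20 v 60 at m = 80. If m is near 120 with equal waits, hardly anyone is left in the 8-week group for this comparison, and the report should then say that the question cannot be answered.

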**Fig. 1 Fig1:**
[figure not shown]
Summary flow chart. The self-report questionnaire packet contains *BAI* Beck’s Anxiety Inventory; *BDI-II* Beck’s Depression Inventory-II; *EQ-5D* Euro-Qol 5D; *RTW-SE* Return to Work Self-efficacy; *MCQ-30* Metacognitive Questionnaire 30; *SHC* Subjective Health Complaints; *RSA* Resilience Scale for Adults; *RTW-E* Return to Work Expectation; *SNAQ* Short Negative Acts Questionnaire; *NAQ-R* Negative Acts Questionnaire Revised; *AUDIT* Alcohol Use Disorders Identification Test; *SAPAS-SR* Standardised Assessment of Personality Self-report. In addition, registry data on sick leave will be collected from 2 years prior to 4 years post intervention

### Eligibility criteria

Participants must:
Be adults of working age (18–67 years)On sick leave either partial or full, due toAnxiety and/or mild to moderate depressive disorders, assessed using MINI International Neuropsychiatric Interview,Eligible for work-related sick leave payouts, andProvide written consent

In addition to the inclusion criteria, participants will be excluded if they are:
Suffering from psychosis (i.e. bipolar disorder, schizophrenia or other psychotic disorders)Engaged in active substance abuseSuffer from cluster A or B personality disorder

### Recruitment process and context

Participants are recruited from the ordinary patient population of *Poliklinikken Raskere tilbake*, a psychiatric out-patient clinic at Diakonhjemmet Hospital in Oslo, Norway. The clinic was originally funded by the national programme “Faster Return” aimed at reducing sick leave and is a part of the national health service. The present study is part of NOR-WORK, the Norwegian studies of psychological treatments and work.

The Norwegian welfare system grants sick-listed employees compensation equivalent to their full salary from the first day of sick leave. This compensation is covered by the employer for the first 16 days of sick leave. The state then covers the compensation from day 17 and up to one full year of sick leave. If an employee is still not able to return to work after a full year on sick leave, they receive a different compensation package equivalent to 66% of their original pay.

Patients are referred by their general practitioners and receive self-report questionnaires by mail before attending a screening session with a clinical psychologist. The treatment is conducted in Norwegian, and the questionnaires are also written in Norwegian. Patients thus have to speak, read and write Norwegian in order to participate. The screening session lasts 60–75 min, and patients are diagnosed based on a clinical assessment which includes the MINI-International Neuropsychiatric Interview.

### Informed consent

Participants are presented with written information on the study and their potential participation by mail prior to their assessment session. The information states clearly the content and purpose of the study, and that any offer of treatment at the clinic is not contingent on participation in any ongoing trials. Patients who do not wish to participate in research, but are eligible for treatment at the clinic, will receive the same treatment from the same group of therapists as those who choose to enrol in the trial. The consent also states clearly what data will be collected, what it will be used for and for how long it will be stored. At the initial assessment session, the therapist also goes through the written consent with the patient, explains the content and answers any questions that the patient may have. Written consent is then signed by both patient and therapist before enrolment in the trial. The informed consent has been evaluated by a representative from the patient interest organisation “Mental Health” and approved by the relevant governing body, the Regional Committee for Medical and Health Research Ethics.

### Randomisation and blinding

After the initial screening session, eligible patients will be randomised using WebCRF, a web-based program provided by the Unit for Applied Clinical Research at the Norwegian University of Science and Technology (NTNU). The block randomisation is stratified on gender and degree of sick leave. The study will include 240 patients in all. Half of the patients will be allocated to the treatment condition (*n* = 120) and the other half to the wait-list conditions (*n* = 120). Half of the patients in the wait-list condition wait 8 weeks, the other half wait 12 weeks before commencing treatment. Because the treatment is offered in an ordinary outpatient clinic, the duration of the treatment will vary. To control for potential differences in treatment duration the wait-list condition also contained two different conditions.

Guidelines from the Norwegian Directorate for Health and Social Affairs state that patients who fulfil the criteria for a moderate depressive episode according to ICD-10 have the right to specialised health care within 8 weeks of referral [45, 46]. Thus, patients with this diagnosis will be allocated evenly between the treatment condition and the 8-week waiting condition. No patients with moderate depressive episode will be allocated to the 12-week waiting condition due to Norwegian law.

The randomisation procedure is performed by administrative personnel who otherwise are not involved in the patient’s treatment. Clinicians are not involved in the randomisation procedure. The initial assessment session is carried out by a different therapist than the one the patient sees for treatment. Blinding the treatment therapist to group allocation is not doable for logistical reasons (e.g. date of journal documents). Assessment of diagnosis at end of treatment using the Mini-International Diagnostic Interview is carried out by an independent clinician who has no prior contact with the patient.

### Outcome measures

#### Primary outcome measures

The primary outcome in the current study is as follows:

##### Beck Depression Inventory-II

BDI-II is a 21 item self-report measure of depression severity over the last 2 weeks. Each of the 21 items is scored from 0 to 3, giving a score range of 0–63. A higher score indicates more severe symptoms. The BDI-II has a Cronbach’s alpha of 0.94 and test-retest reliability of 0.93 [36]. In a previous Norwegian study with patients on sick due to common mental disorders, the Chronbach’s alpha for this measure was 0.89 [34].

##### Beck Anxiety Inventory

BAI is a self-report measure of anxiety severity over the last week. Like the BDI-II, it has 21 items that are scored from 0 to 3, giving a total score ranging from 0 to 63. Higher scores indicate more severe symptoms. The BAI has an alpha of 0.92 and a test-retest reliability of 0.75 [47]. The BAI had a Chronbach’s alpha of 0.90 in a previous Norwegian study of patients on sick leave due to common mental disorders [34].

